#### Satisfaction, evaluation and feasibility

Counselee and counselor satisfaction with both the genetic counseling itself and with the intervention (the latter for the intervention group only) will be assessed using an adapted version as used in a study by Bleiker et al.
[33].

### Sample size and power calculations

We have based the sample size estimates on expected differences between the intervention group and the control group in communication between the genetic counselors and counselees about psychosocial issues. Overall power calculations for estimating sample size requirements were based on the following criteria for defining a substantively meaningful statistical association: (1) power of 0.80, (2) alpha of 0.05, and an (3) effect size “d” of 0.4. With these criteria, 99 cases per study arm are needed, resulting in a total sample size of 198 cases.

We anticipate that approximately 25% of the counselees will not have more than one counseling session and thus will not have a DNA-test disclosure session. Therefore, in order to have sufficient power in the second phase of the trial, we will include 264 participants at the start of the trial.

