## Methods/design

This is a prospective, multicenter, randomized controlled trial in which participants will be randomly allocated to: (1) an intervention group that completes the PAHC questionnaire prior to genetic counseling, the results of which are provided to the genetic counselor; or (2) a control group that completes the PAHC questionnaire, without feedback being given to the genetic counselor. The study consists of two phases. In the first part of the study, the focus is on the efficacy of the intervention during the first face-to-face genetic counseling session. The second phase of the study is concerned with the efficacy of the intervention during a telephone follow-up held approximately 4 weeks after DNA-test results are disclosed in a final face-to-face counseling session.

The primary outcome measures are counselor-counselee communication about psychosocial problems, counselors’ awareness of their counselees’ psychosocial problems, and improved management of those problems. Secondary outcomes include satisfaction with the counseling process, cancer worries, psychological distress, and prevalence of psychosocial problems. The design of the study and the anticipated flow of participants are displayed graphically in Figure 
1.

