### Recruitment and randomization

All eligible counselees will receive an invitation letter from the family cancer clinic, an informed consent form, a baseline questionnaire, and a return envelope three weeks before their first counseling session. Upon returning the completed informed consent form and the baseline questionnaire, we will randomize the participants on a 1:1 basis to either the intervention group or the control group. The minimization method will be used to balance the intervention and control group for each counselor in terms of gender and the cancer syndrome for which genetic counseling is requested
[28]. Neither the counselees nor the counselors will be (or can be) blinded to group assigment.

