### Primary outcome measures

The primary outcomes of the trial are: (1) discussion of psychosocial problems; (2) counselors’ awareness of the counselees’ psychosocial problems; and (3) management of psychosocial problems during and after genetic counseling.

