#### Main research hypotheses

We will evaluate group differences in the number of psychosocial issues discussed during the genetic counseling sessions using analysis of (co)variance. We will assess counselors’ awareness of their counselees’ psychosocial problems by calculating the agreement between counselees’ and counselors’ on their ratings, per domain, of the psychosocial problems experienced by the counselees. We will calculate an Intraclass Correlation Coefficient (ICC2.1.A
[34]) per domain for both the intervention and control group. Group differences will be assessed by treating the ICC’s as Pearson correlation coefficients and using Fisher’s r-to-z transformation to test for statistical differences per domain. Analysis of (co)variance will also be used to evaluate group differences in referral to additional information sources and/or referral to psychosocial care services, and the actual use of such services.

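### Three equal-rank primary outcomes, one of them tested as six separate domain comparisons, have no stated success rule, while the sample size spends the whole 0.05 on communication alone

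*Protocol article*

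**What the plan says.** All references are to the protocol article.

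- **Primary outcomes.** Under Primary outcome measures: "The primary outcomes of the trial are: (1) discussion of psychosocial problems", followed by counselors' awareness and the management of problems. The Background lists a separate hypothesis of a significant effect for each of the three. None is called the lead outcome.
- **Awareness.** Under Main research hypotheses, an intraclass correlation between counselor and counselee ratings is computed in each domain, and the arms are compared by Fisher's r-to-z domain by domain. The section on counselors' awareness gives six domains.
- **Management.** The same section states: "Analysis of (co)variance will also be used to evaluate group differences in referral to additional information sources and/or referral to psychosocial care services", and adds the actual use of services.
- **Phases.** Methods/design: "The study consists of two phases". The first concerns the first face-to-face session and the second the telephone follow-up.
- **Sample size.** The calculation rests on communication, with "power of 0.80, (2) alpha of 0.05, and an (3) effect size" of 0.4, and concludes that "99 cases per study arm are needed, resulting in a total sample size of 198 cases". Enrolment is raised to 264 to power phase II, because "approximately 25% of the counselees will not have more than one counseling session".
- **Discussion time.** The percentage of session time spent on psychosocial issues is described under the primary communication outcome. Time spent on such issues is then listed under Secondary outcome measures and analyzed under Secondary research hypotheses.

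**The concern.** The Background states awareness as one hypothesis, but the analysis yields six p-values and no rule for turning them into one answer. If two domains were significant and four were not, the protocol would not say whether the hypothesis was supported. The same gap exists one level up: three primary outcomes, and no statement whether one, a named one, or all must be significant. The Conclusion ties adoption in practice to proven efficacy without defining proof.

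The single alpha in the document is spent in full on the communication comparison. If the other primary tests are read at the same level and any positive result is taken as success, a questionnaire with no effect has well over a 5% chance of being reported as efficacious on a primary outcome. The overlap between primary and secondary on discussion time makes the edge of the primary family harder still to draw.

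**Working it through.** **1. Reproduce the sample size.** Inputs from Sample size and power calculations: d = 0.4, power 0.80, alpha 0.05. Allocation is 1:1 (Recruitment and randomization). Sidedness is not stated.

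- Two-sided: n = 2(1.960 + 0.842)² / 0.4² = 98.1, rounded up to 99 per arm. The t-based solution is 99.08.
- One-sided: 78 per arm, which does not match.
- Enlargement for phase II: 198 / (1 − 0.25) = 264.

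The stated figures are reproduced, and only with an undivided two-sided 0.05 for one outcome.

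**2. Count the phase I primary tests.**

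- Communication, number of issues discussed: 1.
- Awareness, one per domain: 6.
- Management: 1 if referral to information or care is one combined outcome and service use is not tested separately; 3 if information, care and service use are separate.
- Total: 1 + 6 + 1 = 8, up to 1 + 6 + 3 = 10.

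The narrowest count, with awareness reduced to one test and management to one, is 3.

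**3. Chance of at least one false positive**, if each test uses two-sided 0.05, no effect exists and any significant result counts. Under independence it is 1 − 0.95^k. For a common correlation ρ, take Z_i = √ρ·C + √(1−ρ)·E_i, with C and E_i independent standard normal, and find P(max|Z_i| > 1.96). The documents give no correlation, so ρ is assumed and a range is shown.

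| Tests | ρ = 0 | ρ = 0.5 | ρ = 0.8 |
|---|---|---|---|
| 3 (one per hypothesis) | 14% | 13% | 10% |
| 6 (awareness domains alone) | 26% | 21% | 14% |
| 8 | 34% | 25% | 16% |
| 10 | 40% | 29% | 17% |
| 18 (two phases, upper reading) | 60% | 40% | 22% |
| 20 (two phases, upper reading) | 64% | 42% | 22% |

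**4. Price of control over three hypotheses.** Power ≈ Φ(d·√(n/2) − z), with z = 1.960 at 0.05 and 2.394 at 0.05/3.

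- Phase I, 264/2 = 132 per arm: 0.4·√66 = 3.250. Power is Φ(1.290) = 0.90 at 0.05 and Φ(0.856) = 0.80 at 0.05/3.
- Phase II, 99 per arm: 0.4·√49.5 = 2.814. Power at 0.05/3 is Φ(0.420) = 0.66.

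The t-based values are 0.899, 0.799 and 0.655. All apply to d = 0.4, which was set for communication only.

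**The case against.** **0.05 is a planning value.** A reader might infer that the protocol tests every primary outcome at 0.05 and that its stated alpha is therefore false. The text does not support this. The value appears once, as a sizing criterion for communication; the analysis sections give no threshold; and nowhere is 0.05 called a familywise rate. As a per-comparison level for communication it is valid and reproduces the sample size. This objection stands, so the error rates above are conditional on how the tests are read.

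**The analysis plan may settle it.** Multiplicity procedures are often left to a statistical analysis plan, and silence in a condensed article would not be a finding. This stands for the adjustment method itself. It does not cover what the article fixes: three equal-rank primaries, a single awareness hypothesis tested domain by domain, and a sample size that leaves no alpha for the rest.

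**The count can be inflated.** A reader might infer 18–20 primary tests and an error of 60–64%. That needs every test to be repeated in phase II, which Main research hypotheses does not say, and it needs independence. The domain ratings come from the same checklist and questionnaire, and the Background describes communication, awareness and management as a cascade, so positive correlation is expected. The case must rest on 3 to 10 tests in phase I.

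**Separate aims may be judged separately.** Some statisticians defend unadjusted inference on distinct, pre-named aims, and a requirement that all three be significant would not inflate error across outcomes. But no such rule is stated, and either position still leaves the six awareness results without a combination rule.

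**Conclusion.** The point holds as a badly fixed primary analysis; it does not show that a stated error rate is false. The awareness hypothesis cannot be decided from the analysis described, and familywise control across the three primary outcomes is not shown. If each test uses 0.05 and any significant primary result counts, the phase I false-positive chance is about 10–14% for three tests, 14–26% for the awareness domains alone and 16–40% for 8–10 tests. Those ranges rest on assumed common correlations from 0.8 down to 0. Even the most favorable case shown, three tests at correlation 0.8, is about double 5%. The two-phase figures are an upper reading and should not carry the argument.

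**What to change.** 1. For the first session, prespecify one test per primary hypothesis:
   - the number of issues discussed;
   - one overall test of counselor–counselee agreement across the six domains, for example a permutation test of the mean difference between arms in Fisher-z agreement;
   - any referral to information or psychosocial care.
2. Apply Holm across these three, or a fixed order starting with communication, the outcome that sized the trial.
3. Report per-domain agreement, service use and percentage of session time as supporting results. Reconcile the description of the primary communication outcome with Secondary outcome measures and Secondary research hypotheses on discussion time.
4. State phase II as a separate, later family with its own declared role. Demoting it without comment would conflict with the enlargement to 264 made to power it. If it also needs control over three outcomes, restate its power as about 0.66 at 0.05/3 with 99 per arm.

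**Cost.** Phase I needs no additional participants. Single-domain results are no longer confirmatory. Phase I power for d = 0.4 falls from 0.90 to about 0.80 at the strictest Holm step; a fixed order would keep communication at the full 0.05. Power for awareness and referral is unknown under any of these schemes, because the article gives no effect size for them.

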### Intervention group procedure

Within the Netherlands, individuals seeking cancer genetic counseling routinely undergo a first consultation with a genetic counselor or a clinical geneticist and, when opting for a DNA-test, a final counseling session during which the DNA-test results are disclosed to the counselee. If indicated, screening recommendations for the patient and relatives are discussed within these sessions. The study intervention will take place within this standardized process, at the time of the first face-to-face genetic counseling session (phase I), and by telephone 4 weeks after the final face-to-face counseling session (phase II). The participants in the intervention group will be asked to complete the PAHC questionnaire either via the internet or, if preferred, by mail shortly before the face-to-face and the telephone follow-up counseling sessions. The counselee’s responses to the PAHC questionnaire will be made available to the genetic counselor prior to the counseling sessions.

The PAHC questionnaire consists of 26 questions addressing psychosocial problems and worries that are specifically relevant to counselees within the cancer genetics counseling and testing setting. The content of the PAHC questionnaire is organized into the following six domains: (1) hereditary predisposition; (2) family- and social issues; (3) practical issues; (4) general emotional issues; (5) cancer-specific issues; and, for those who have children 6) children-specific issues. The number of items per domain varies between 2 and 7. All 26 items are scored on a 4-point, Likert-type scale ranging from 1 (“not at all”) to 4 (“very much”). The PAHC questionnaire is supplemented by the Distress Thermometer (DT), a visual analogue scale ranging from 0–10 (no distress-severe distress). The timeframe of the PAHC questionnaire and the DT is the previous week. Per problem domain assessed by the PAHC questionnaire, the respondent is asked to indicate whether (s)he would like to receive professional psychosocial support
[25].

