**Counselees**		
*Baseline (first) questionnaire*	Cancer worries	Before randomization
	General distress	
	Demographic data	
*Second questionnaire (T1)*	Evaluation of screening instrument	4 weeks after genetic counseling, before final consult, end of phase I
	Evaluation of counselor	
	General distress	
	Need for extra support	
	Cancer worries	
*Third questionnaire (T2)*	Specific psychosocial problems	4 months after the telephone call,
	Need for extra support	end of phase II
	Cancer worries	
	Evaluation of screening instrument	
	Satisfaction	
	General distress	

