### Statistical analyses

All analyses will be performed on an intention-to-treat basis. Missing data on the HADS and CWS will be imputed using half-scale mean substitution methods. Data of participants who complete and return their first follow-up questionnaire after their final counseling session will be omitted from the analysis, because knowing the DNA-test result might influence questionnaire responses. Between rater agreement on the audiotaped sessions will be assessed by calculating the percentage of absolute agreement. Effect sizes will be calculated using standard statistical approaches.

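### The blanket intention-to-treat statement does not hold for phase II, which follows only counselees who reach DNA-test disclosure, an event settled after randomization

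*Protocol article*

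**What the plan says.** Under Statistical analyses, the article makes a statement without exception: "All analyses will be performed on an intention-to-treat basis". The same paragraph then omits first follow-up questionnaires (T1) that are returned after the final session.

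The schedule is as follows.

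- **Randomization** takes place when the consent form and baseline questionnaire come back, before the first session (Recruitment and randomization).
- **Phase I** is the first face-to-face session. A final session exists "when opting for a DNA-test, a final counseling session during which the DNA-test results are disclosed" (Intervention group procedure).
- **Phase II** is a telephone session about 4 weeks after that final session (Methods/design; Intervention group procedure).
- **T2** is set at "4 months after the telephone call" (Table 1). It carries specific psychosocial problems, need for support, cancer worries, satisfaction and general distress.

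Sample size and power calculations expects that "approximately 25% of the counselees will not have more than one counseling session and thus will not have a DNA-test disclosure session" and concludes: "in order to have sufficient power in the second phase of the trial, we will include 264 participants at the start of the trial".

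**The concern.** An intention-to-treat comparison keeps everyone in the arm to which they were randomized. On this schedule, a counselee without a disclosure session has no telephone call, so there is no phase II session to code and no date from which to time T2. The one imputation rule given, half-scale mean substitution for HADS and CWS, fills items missing within a questionnaire. It cannot stand in for an assessment that was never scheduled.

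Entry to phase II is settled after randomization and at least partly by counselees opting for a test. The phase I feedback comes at the first session of that process and is meant to bring worries about heredity, family and cancer into the discussion. If it changes how many counselees go on, or which ones, the phase II arms would differ in worry and problems before the telephone call. Hypotheses 6 and 7, as far as they concern the period after counseling, would then be answered in a selected subset under a label that promises full randomized protection. Use of psychosocial services as reported at T2 is in the same position.

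**Working it through.** **Step 1. Reproduce the plan's figures.** Inputs, all from Sample size and power calculations: "power of 0.80, (2) alpha of 0.05" and "effect size “d” of 0.4". Sidedness is not stated, so two-sided is taken here.

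n per arm = 2 × (1.960 + 0.842)² / 0.4² = 2 × 7.849 / 0.16 = 98.1, which rounds up to 99 (the t-based solution is 99.08). One-sided alpha would give 78. This matches "99 cases per study arm are needed, resulting in a total sample size of 198 cases".

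Inflation: 198 / (1 − 0.25) = 264. This also matches.

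**Step 2. Identify the phase II set.** 264 × 0.75 = 198 = 2 × 99. Phase II is sized on counselees who reach disclosure, and 264 − 198 = 66 randomized participants lie outside it. The arithmetic is right. It is the description of the analysis set that does not fit.

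**Step 3. How large could the selection effect be?** The documents give no continuation rates by arm, so these inputs are assumptions: average continuation of 75%, a gap between arms of 0, 5 or 10 points centred on 75%, a normally distributed latent propensity to continue with correlation r of 0.3 to 0.5 with the outcome, and no true effect.

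The mean outcome among those who continue is shifted by r × λ(p), where λ(p) = φ(Φ⁻¹(p)) / p. The spurious difference between arms is r × [λ(p_low) − λ(p_high)].

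| Gap | λ(p_low) − λ(p_high) | r = 0.3 | r = 0.5 | Type I error (nominal 0.05) |
|---|---|---|---|---|
| 0 | 0 | 0 | 0 | 0.050 |
| 5 points (72.5% v 77.5%) | 0.4602 − 0.3870 = 0.073 | 0.022 SD | 0.037 SD | 0.053 to 0.058 |
| 10 points (70% v 80%) | 0.4967 − 0.3500 = 0.147 | 0.044 SD | 0.073 SD | 0.061 to 0.081 |

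The type I error uses the standard error √(1/(132 p_low) + 1/(132 p_high)), about 0.142 SD.

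**Step 4. Could the trial see such a gap?** With 132 per arm, the standard error of the difference in continuation is √(2 × 0.75 × 0.25 / 132) = 0.053, so the 95% interval is about ±10.4 points. A gap of 5 to 10 points would often go unresolved. That reflects the sample size and is not evidence that a gap exists.

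**Step 5. What the planned adjustment covers.** Under Secondary research hypotheses, worry and distress are analysed by analysis of covariance with previous scores as covariate. Selection acting through earlier worry or distress would be partly removed there, so the figures in step 3 are before adjustment. The logistic regression for specific problems has no covariate named, so they apply to hypothesis 7 without that reduction.

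**The case against.** The strongest reply has four parts.

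1. **The exclusion is inferred.** No sentence says that the 25% are dropped, and a condensed article may leave their handling to the full protocol. The first half is correct. But the point rests on what the article does state: a universal claim, a T2 clock that starts at the call, and a phase II sample size equal to the subset. Those cannot all stand together.
2. **The reasons for stopping after one session are not given.** A reader might infer that all 25% decline testing by choice, under the influence of the intervention. The documents do not support that. They describe testing as something counselees opt for, but do not say when the decision is made or whether everyone is offered a test. The label fails whatever the reason, whereas the bias would need the intervention to affect who continues.
3. **A subset is partly unavoidable.** Discussion, awareness and management during the call cannot be measured without a call, and Methods/design openly defines phase II around it. This stands for the session outcomes. It does not apply in the same way to self-reported worry, distress, problems and service use, which do not depend on a call in principle. T1 already measures worry and distress without one.
4. **The effect is small and rests on assumptions.** This also stands. A reader might set the upper value against d = 0.4 and quote a share of the planned effect, but d = 0.4 was set for communication, not for worry or distress, so the comparison is not apt.

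**Conclusion.** The intention-to-treat statement is too broad. Phase II comparisons are conditional on reaching disclosure, which is expected for about 198 of the 264 randomized. The T1 analysis falls short of the label as well, because late-returned first follow-up questionnaires are omitted on a post-randomization criterion.

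It would go too far to say that phase II is biased. With equal continuation by arm, the selection model gives no bias. Under assumed gaps of 5 to 10 points and correlations of 0.3 to 0.5, the spurious difference is about 0.02 to 0.07 SD before adjustment, with type I error at most about 0.08. Equal proportions would be reassuring but not conclusive, since the kind of counselee who continues could still differ by arm.

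The primary comparisons at the first session and the sample-size figures are not affected.

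**What to change.** 1. Reserve the term intention-to-treat for analyses that keep all randomized participants. Apply the same limit to the T1 analysis from which late questionnaires are omitted.
2. Pre-specify a comparison between arms of the proportion reaching DNA-test disclosure, with a confidence interval.
3. Describe phase II as a comparison among counselees who reached disclosure. Adjust it for pre-randomization variables already collected: baseline CWS and HADS, cancer history, known family mutation and the minimization factors. Include these in the logistic regression for specific problems. For T2 worry and distress, name the baseline score as the covariate, since previous scores could also mean T1.

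The cost is one extra table, some rewording and a narrower phase II conclusion. No new data are needed.

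Sending T2 to the roughly 66 counselees without a disclosure session is optional. It would allow worry and distress to be analysed in everyone randomized, but a time point would have to be defined, because the article gives none that does not depend on the call. It could also dilute the contrast: if those 25% had no effect, an effect of 0.4 would become 0.4 × 0.75 = 0.30, with power of about 0.68 at 132 per arm.
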